### **3.0. Literature review**

#### **Occurrence of dental caries, periodontal conditions and oral impacts on daily performance among adolescents**

Dental caries affect about 19-93.7% of adolescents globally and its distribution varies by demographic and social factors (Aldosari et al., 2004, Mtaya et al., 2009, Nurelhuda et al., 2009, Mashoto et al., 2010, Singh., 2011, Pakpour et al., 2011, Krisdapong et al., 2013, Al-Darwish et al., 2014, Mathur et al., 2014, Dye et al., 2015, Vernazza et al., 2016, Msyamboza et al., 2016, Lage et al., 2017, Borges et al., 2017, Giacaman et al., 2018, Simangwa et al., 2018, Simushi et al., 2018, Clark et al., 2019). The prevalence ranges from 41-72% in Europe and America (Jamelli et al., 2010, Dye et al., 2015, Lyra et al., 2015, Vernazza et al., 2016, Borges et al., 2017, Lage et al., 2017, Giacaman., 2018), 20.0-93.7% in Asia (Al-Sadhan, S., 2006, Pakpour et al., 2011, Krisdapong et al., 2013, Mathur et al., 2014, Al-Darwish et al., 2014,) and 8.8%- 50.98% in Africa (Nurelhuda et al., 2009, Mashoto et al., 2010, Singh., 2011, Msyamboza et al., 2016, Simagwa et al., 2018, Simushi et al., 2018). While some studies in Europe and America report no significant difference in caries occurrence by age and sex (Dye et al., 2015, Borges et al., 2017, Lage et al., 2017, Clark et al., 2019), others report significantly more girls than boys (Vernazza et al., 2016) and older than younger adolescents (Dye et al., 2015, Lyra et al., 2015) are affected. The disease also significantly affects more adolescents in rural than urban areas (Lyra et al., 2015, Borges et al., 2017, Giacaman., 2018) and those from larger than smaller family sizes (Lyra et al., 2015). In Africa and Asia, the disease affects significantly more girls than boys (Al-Sadhan, S., 2006, Al-Darwish et al., 2014, Msyamboza et al., 2016,), older than younger adolescents (Al-Darwish et al., 2014, Simagwa et al., 2018), and those from lower than higher socioeconomic status (Nurelhuda et al., 2009, Pakpour et al., 2011, Mathur et al., 2014, Krisdapong et al., 2013). The disease also affect significantly more urban than rural adolescents (Nurelhuda et al., 2009, Owino et al., 2010, Simushi et al., 2018), however Mashoto et al., (2010) and Mapengo et al., (2010) reported the opposite and Msyamboza et al., (2016) reported no difference.

Proportion of adolescents with plaque ranges from 3.5-27.2% in Europe and America (Vadiakas et al., 2012, Botero et al., 2015, Giacaman et al., 2018) and 16.1-81.1% in Asia and Africa (Yazdani et al., 2009, Mbawala et al., 2010, Berhane et al., 2014, Sukhabogi et al., 2014, Oyedele et al., 2018, Simangwa et al., 2018). The proportion is significantly higher in older, males, and those from rural and low socioeconomic status in all regions (Mbawala et al., 2010, Vadiakas et al., 2012, Oyedele et al., 2018, Simangwa et al., 2018, Giacaman et al., 2018). Plaque is also reported in Africa and Europe to be more among adolescents from lower than higher fathers or mother's education (Mbawala et al., 2010, Vadiakas et al., 2012, Berhane et al., 2014).

Prevalence of gingivitis among adolescents range from 16.7-72.8% in Europe and America (Vadiakas et al., 2012, Botero et al., 2015, Chrysanthakopoulou et al., 2020), 59-100% in Asia and middle east (Sharva et al., 2014, Sukhabogi et al., 2014) and 26.7-40.9% in Africa (Azodo et al., 2015, Simangwa et al., 2018). Gingivitis affects significantly more adolescents in rural than urban areas, males than females (Vadiakas et al., 2012, Nuaimi et al., 2014, Simangwa et al., 2018), those from low socio-economic status families and parents with low education (Mbawala et al., 2010, Vadiakas et al., 2012, Sharva et al., 2014) in all regions. Information on clinically assessed gingivitis among Zambian adolescents could not be retrieved, however a self reported experience of gingivitis is 19% (Hagberg and Sjodahl 2007).

Impact of oral diseases on daily performance is reported by 38.5-88.7% of adolescents in Europe and America (Bianco et al., 2010, Cortes-Martincorena et al., 2010, Castro et al., 2011), 44-89.8% in Asia (Usha et al., 2011, Krisdempong et al., 2013, Amilani et al., 2020), 28.6-56.5% in Africa (Mtaya et al., 2007, Nurehulda et al., 2010, Chukumwa et al., 2016). The proportion of Zambian adolescents reporting oral impacts on daily performance vary widely from 11.7- 61.5% (Andersson et al., 2017, [name] et al., 2018). Oral impacts are reported more by girls than boys, those from higher than lower socio-economic status, and urban than rural adolescents (Mtaya et al., 2007, Mashoto et al., 2009, Nurehulda et al., 2010, Mbawala et al., 2011, Chukumwa et al., 2016, [name] et al., 2018). Difficulties on eating and cleaning mouth are the commonly reported impacts (Mtaya et al., 2007, Mashoto et al., 2009., Nurehulda et al., 2010, Bianco et al., 2010, Cortes-Martincorena et al., 2010, Castro et al., 2011, Mbawala et al., 2011, Usha

et al., 2011, Chukumwa et al., 2016). Additionally, difficult in smiling and emotion disturbances are mostly reported impacts among European and American adolescents (Bianco et al., 2010, Cortes-Martinicorena et al., 2010, Castro et al., 2011) while speaking difficulties is reported in Africa and Asia (Mtaya et al., 2007, Usha et al., 2011).

Available information on oral disease occurrence in terms of magnitude and distribution among African adolescents was published about a decade ago. The prevailing changes in lifestyles make these disease states not suitable for extrapolation in Zambian adolescents to sufficiently inform the government in making appropriate oral health plans for this group.

### **Adolescent's oral health knowledge and related behaviours**

The proportion of adolescents with knowledge on sugar containing food as a cause of tooth decay is reported to range from 50-86.5% in Europe and America (Smyth et al., 2007, Graça et al., 2019), 27.5-69.4% in Asia (Lian et al., 2010, Dixit et al., 2013, Hague et al., 2016) and 48.2%-94.6% in Africa (Oredugba et al., 2004, Mashoto et al., 2009, Okemwa et al., 2010, Mbawala et al., 2010, Nyamuryekung'e, 2012). The proportion of those with knowledge on the importance of regular tooth brushing ranges from 19-98.1% in all regions (Oredugba et al., 2004, Shenoy et al., 2010, Dixit et al., 2013, Hague et al., 2016, Graça et al., 2019). It is 33-71% in Europe and America (Smyth et al., 2007, Graça et al., 2019), 19.0-57.4% in Asia (Lian et al., 2010, Shenoy et al., 2010, Dixit et al., 2013) and 65-98.1% in Africa (Darout et al., 2005, Carneiro et al., 2011, Varenne et al., 2006). Percentage of adolescents with knowledge on use of fluoridated toothpaste as a means of preventing dental caries ranged from 40.5-75.3% in Europe and America (Smyth et al., 2007, Graça et al., 2019), 18-83.7% in Asia (Lian et al., 2010, Dixit et al., 2013, Sanadhya et al., 2014, Hague et al., 2016) and 6-87.7% in Africa (Varenne et al., 2006, Carneiro et al., 2011, Elzahaf et al., 2019). Percentage of adolescents with knowledge on importance of dental check up at least once a year range as follows 35.4-50% in Europe and America (Smyth et al., 2007, Graça et al., 2019) and 42-98.1% in Asia and Africa (Blaggana et al., 2016, Al-Hussaini et al., 2003, Carneiro et al., 2011, Varenne et al., 2006)

The proportion of adolescents practicing good oral health related behaviours in Europe and America are; 62-100% for regular tooth brushing (Ericsson et al., 2012, Smyth et al., 2007, Veiga et al., 2014, Bombert et al., 2018, Graça et al., 2019), 4.-14.4 % for flossing (Ericsson et al., 2012, Veiga et al., 2014, Bombert et al., 2018, Graça et al., 2019 ) 26-41% for sugar consumption of less than five times a day (Smyth et al., 2007, Graça et al., 2019), 39.2.-75% for dental check up at least once a year (Vadiakas et al., 2012, Veiga et al., 2014, Bombert et al., 2018, Graça et al., 2019) and more than 90% report to use fluoridated toothpaste (Bombert et al., 2018, Graça et al., 2019). In Asia 37.5-95.7% of adolescents brush their teeth regularly (Zhu et al., 2003, Lian et al., 2010, Hague et al., 2016, Asubaie et al., 2019), 0-6.6% floss (Pakpour 2011, Subaie et al., 2019), 9.3%-24.9% consume sugar containing foods less than five times a day (Zhu et al., 2003, Lian et al., 2010), 36.6-43.9% attend dental check up at least once a year (Zhu et al., 2003, Pakpour 2011, Asubaie et al., 2019) and 4.5-89.8%. to use fluoridated toothpaste (David et al., 2005, Bhardwaj et al 2013., Hague et al 2016) and only 12.7% change tooth brushes after every three months or when bristles flair (Hague et al 2016). In Africa, 62.2-92% of adolescents are reported to brush their teeth regularly (Oredugba et al., 2004, Mbawala et al., 2010, Okemwa et al., 2010, [name] et al., 2018), 0.3 -11.3% to floss (Carneiro et al., 2011, Azodo and Agbor 2015, Elzahaf et al., 2019), 38.8-91.3% to consume sugar containing foods less than five times a day (David et al 2005, Carneiro et al., 2011, [name] et al., 2018), 12.6-.53% attend for dental check up at least once a year (Oredugba et al., 2004, Mbawala et al., 2010, [name] et al., 2018) and 38.9-81.3% use fluoridated toothpaste (Okemwa et al., 2010, Elzahaf et al., 2019). Good adolescents' oral health related behaviours are reported significantly more in females than males (Okemwa et al., 2010, Carneiro et al., 2011, Bombert et al., 2018) older than younger ([name] et al., 2018), those from urban than rural, from higher than lower socio-economic status families (Mashoto et al., 2010, Bombert et al., 2018, [name] et al., 2018) and whose parents have higher than lower education level ([name] et al., 2018, Bombert et al., 2018). Information on oral health knowledge and behaviors among Zambian adolescents is scarce. Only McKittrick and Jacobsen, (2014) and Hamonga et al., (2015) reported 10% and 71.9% as the proportion of adolescents practicing tooth

brushing twice a day or more respectively. Other elements of knowledge and behaviors could not be retrieved.

### **Effects of Oral Health Education (OHE) on adolescents' oral health knowledge and related behaviours**

Improvement in knowledge following OHE has been reported to be; 46-100% for tooth brushing (D'Cruz *et al.*, 2013, Sanadhya *et al.*, 2014, Hague *et al.*, 2016, Vangiparum *et al.*, 2016, Naidu *et al.*, 2017), 40.1-98.9% for sugar containing food/drinks as cause of tooth decay (Sanadhya *et al.*, 2014, Hague *et al.*, 2016, Naidu *et al.*, 2017) and 31.5-52.2% on the role of fluoridated tooth paste (Sanadhya *et al.*, 2014, Hague *et al.*, 2016).

Improvement in tooth brushing frequency following OHE is reported to range from 23 to 47% (Haque *et al.*, 2016; Pakpour *et al.*, 2016; Melo *et al.*, 2018, Esan *et al.*, 2015, [name] *et al.* 2012), reduction in risky sugar consumption 28.8-31% (Haque *et al.*, 2016, Naidu and Nandlal, 2017 Esan *et al.*, 2015), regular use of fluoride toothpaste 26-42% (Melo *et al.*, 2018, Wickreasinghe and Ekanayake, 2017, Hague *et al.*, 2016) and 26% for regular preventive dental check-ups (Wickremasinghe and Ekanayake, 2017). However, other researchers found no statistical significant improvement in; regular dental visit (Dudovitz *et al.*, 2018), reduction in risky sugar consumption (Wickremasinghe and Ekanayake, 2017, Dudovitz *et al.*, 2018) and regular use of fluoride toothpaste (Yang *et al.*, 2009). The available information is inconclusive with some studies reporting improvement in adolescents' knowledge and behaviours following OHE intervention while others not.

### **Effects of Oral Health Education (OHE) on adolescents' plaque score**

Six months to three years OHE interventions on reducing plaque have been conducted using different methods such as classroom sessions and demonstrations (Yekaninejad *et al.*, 2012, Haleem *et al.*, 2012, Reddy *et al.*, 2016), supervised tooth brushing (Hilgert *et al.*, 2015) or combined strategies. A wide range of improvement (8 to 67%) in adolescents' plaque score following OHE has been reported (Haleem *et al.*, 2012, Yekaninejad *et al.*, 2012, D'Cruz and Aradhya, 2013, Hilgert *et al.*, 2015, Reddy *et al.*,

2016, Naidu and Nandlal, 2017) though other authors did not find significant improvement (Frencken et al., 2001, [name] et al., 2012). The effectiveness of OHE in plaque score reduction was reported by Hallem et al., (2016) to be influenced by mode of delivery, repetitive sessions and reinforcement of messages. Observed wide range of effect of OHE on plaque score may have been due to lack of consistence on study duration, mode of oral health delivery and intentional planned OHE intervention activities.

### **Effects of Oral Health Education (OHE) on adolescents' gingival bleeding score**

Different OHE methods such as classroom sessions and demonstrations (Mbawala et al., 2012, Yekaninejad *et al.*, 2012, Gauba et al 2013) supervised tooth brushing (Hilgert *et al.*, 2015) or combined strategies have been used to deliver OHE and resulted in reduction of gingival bleeding among adolescents. The follow up duration varied from 3 weeks to 2 years. The interventions achieved 10.3-50% reduction in the proportion of adolescents with gingival bleeding (Biesbrock et al., 2003, Ganesh et al., 2007, Mbawala et al., 2012, Yekaninejad *et al.*, 2012, D'Cruz and Aradhya, 2013, Gauba et al 2013). Reduction in bleeding score is reported significantly more in females than males and urban than rural adolescents (Mbawala et al., 2012). Most OHE messages used in the cited literature did not specifically target prevention of gingivitis. Additionally, socio-demographic differences in gingival bleeding reduction was not assessed by most authors.

### **Effects of BPOC on adolescents' dental caries status**

Oral Health Education interventions intending to reduce dental caries with duration of 6 months to 3.5 years have been conducted (Frencken et al., 2001, Mbawala et al., 2012, Haque *et al.*, 2016, Stein *et al.*, 2018). Haque *et al.*, (2016) and Qudri et al., (2018) report 25% and 35% respectively, reduction in dental caries following OHE while others did not find conclusive evidence to support effectiveness of OHE in reducing dental caries.

Tooth brushing interventions with a follow up time ranging from 6 months to 3 years have been conducted through supervised (Hilgert *et al.*, 2015, Petersen *et al.*, 2015, Clark *et al.*, 2019) and unsupervised methods (Marinho et al., 2003, Kumar et al., 2016, van der

Walt et al., 2018). The interventions reduced the proportion of adolescents with dental caries in a range of 24-50%. Frequency of toothpaste use is reported to influence the effectiveness of fluoride toothpaste in caries prevention. A systematic review reports an average of 24% reduction in decayed, missing and filled tooth surface as a result of use of fluoridated tooth paste (Marinho et al., 2003). No age and sex differences in caries reduction are reported (Clark *et al.*, 2019). No information was accessed where both OHE and fluoride toothpaste were used as a package in caries prevention interventions.

### **Effects of BPOC on adolescents' OHRQoL**

No information reporting effect of BPOC as a package on adolescents' OHRQoL could be accessed. Available studies reporting effects on adolescents' OHRQoL used OHE, ART and/or OUT. Applying ART and OUT to school adolescents, Mashoto et al., (2010) reported 13.7% improvements in overall adolescents' oral impacts with minimal effect size in eating speaking, cleaning, smiling, emotion disturbance, school work and social role. Whereas Chukwumah et al., (2016) in a dental facility-based study reported an overall marked improvement in oral impacts; the effect size was moderate to large for all domains ranging from 0.2 for smiling and participating in social role to 0.9 for eating. No significant differences in oral impacts improvement by age, sex or socio-economic status was reported (Chukwumah et al., 2016).

### **Effects of modified BPOC on adolescents' socio-demographic differences in oral health status and OHRQoL**

Pattussi et al. (2006) and [name] et al., (2012) reported that provision of oral health education achieved reduction of inequalities in dental caries and gingival health among adolescents of Brazil and Tanzania, respectively. However, Qadri *et al.*, 2018 reported widening of socio-economic disparity in caries; caries reduction being more among adolescents from high SES families while other investigators state that the effect of OHE in reducing oral health inequalities is inconclusive (Polk et al., 2010, Roncalli *et al.*, 2015). No findings could be accessed reporting changes of socio-demographic inequalities in oral health status and related quality of life following ART and OUT.

#### **4.0. Materials and Methods**

##### **4.1. Study design**

This will be a cluster randomized controlled field trial to assess the effectiveness of applying the WHO basic package of oral care (BPOC) and oral health education in improving oral health knowledge and related behaviors, oral health and OHRQoL among adolescents in Copperbelt, Zambia.

##### **4.2. Study area**

The study will be conducted in Copperbelt province, the second highly populated province in Zambia after Lusaka with a total population of 2,542,132 out of which 24% are adolescents. Administratively the province is divided into 10 districts with a total number of 102 government and private secondary schools located in both rural and urban set up. Copperbelt residents engage in different economic activities such as mining and quarrying, light industry manufacturing, animal keeping and small- and large-scale farming which can account for differences in socio-economic status. Socio-demographic mix of adolescents in the Copperbelt province provides a typical representation of Zambian adolescents and therefore enables inference of the results to the whole country at large.

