## **Definition of key terms**

### **Adolescent**

World Health Organization (WHO) defines an adolescent as any person between ages 10 and 19, although other sources incorporate a span of 9 to 26 years (Curtis, A.C., 2015). WHO definition will be adopted in this study.

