### **2.2. Specific Objectives**

- 1 To determine prevalence and distribution of dental caries, periodontal conditions and oral impacts on daily performance among adolescents in Copperbelt Province, Zambia
- 2 To determine the association between dental caries and oral health related quality of life among adolescents in Copperbelt Province
- 3 To assess the effects of a six months modified basic package of oral care intervention on knowledge and behaviors related to dental caries after 18 and 24 months of follow up.
- 4 To assess the effects of a six months modified basic package of oral care intervention on prevalence of dental caries after 18 and 24 months of follow up
- 5 To assess the effects of a six months modified basic package of oral care intervention on prevalence of oral impacts on daily performance after 18 and 24 months of follow up

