##### **4.3. Study population**

The study will involve adolescents aged 10-14 years in their first year of secondary school in Copperbelt Province, Zambia. Adolescence is an important phase of life which marks transition from childhood to adulthood and oral health related behaviors acquired during this phase affect their current and future oral health. Adolescents' oral health status and related behaviors are directly dependent on their family's socio-economic status and therefore the effect of any socioeconomic gradient in health is likely to be reflected in this group.

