#### **4.5. Sampling**

A two-stage cluster sampling technique will be used; district being a sampling unit at stage one and secondary schools at stage two. Through simple random sampling, three out of ten districts of Copperbelt province will be selected and from each district a total of six clusters (secondary schools) will thereafter be selected as part of the study. To attain a sample size of 1,760 participants, 18 clusters with cluster size of 90-100 will be involved. All adolescents aged 10-14 in grade 8 at selected clusters will be eligible to participate in this study.

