#### **4.8. Inclusion and exclusion**

##### **4.8.1. Cluster level**

*Inclusion criteria*

- Secondary within Copper belt providence with grade 8 students

*Exclusion criteria*

- Schools involved in any other oral health intervention programs
- Boarding schools
- Single sex schools
- Special need schools

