#### **4.12. Data entry cleaning and analysis**

Data entry, coding and processing will be done using a computer software program IBM SPSS for Windows (Version 23). Frequency distribution for proportions, means (SD), cross tabulation with chi –square and binary logistic regression reported in odds ratio and 95% (CI) will be performed per respective objectives.

Frequency distribution for proportions of adolescents with plaque, gingival bleeding, poor oral health behaviors and oral health related quality of life. Dental caries experience will be summarized as number and percentage. Furthermore, cross tabulation for bivariate comparison of differences in intervention outcome variables by socio-demographics, study arms and oral health behaviors will be conducted. To examine for the differences between the groups (effectiveness of trial intervention) generalized estimating equations will be performed and reported in odds ratio and 95% confidence interval. A statistical significance difference shall be assumed when  $p \leq 0.05$ . Analysis plan per objective is summarized in appendix 6.

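### Objective 1 and Section 4.2 claim Copperbelt adolescents and all of Zambia, but only grade 8 pupils in eligible mixed day schools can be sampled, and no weighting is specified for a fixed take of schools per district

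*Protocol*

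**What the plan says.** Three places in the Protocol state the target. Objective 1 in Section 2.2 reads "To determine prevalence and distribution of dental caries, periodontal conditions and oral impacts on daily performance among adolescents in Copperbelt Province, Zambia". The definition of key terms adopts the WHO meaning of adolescent, "any person between ages 10 and 19". Section 4.2 says "Socio-demographic mix of adolescents in the Copperbelt province provides a typical representation of Zambian adolescents" and that this "enables inference of the results to the whole country at large".

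Other sections state who can be sampled.
- Section 4.3 gives the study population as "adolescents aged 10-14 years in their first year of secondary school". Sections 4.5 and 4.8.2 confirm grade 8.
- Section 4.8.1 excludes "Single sex schools", boarding schools, special-need schools and schools already in another oral health programme.
- Section 4.8.2 excludes pupils with anodontia, severe fluorosis, past orthodontic treatment or special needs.
- Section 4.5 says "three out of ten districts of Copperbelt province will be selected and from each district a total of six clusters (secondary schools", with every grade 8 pupil aged 10 to 14 in a chosen school eligible. Section 4.7 works with four schools per district.

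For the descriptive results, Section 4.12 names "Frequency distribution for proportions of adolescents with plaque, gingival bleeding, poor oral health behaviors and oral health related quality of life" and gives caries as number and percentage. Appendix 6 lists frequencies, chi-square tests and logistic regression for Objective 1. Neither mentions sampling weights.

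**The concern.** The population named in the objective, and the country named in Section 4.2, are both wider than the population that the design can reach. The result is meant to be used: Section 1.4 says that the study will show the magnitude of caries and gingivitis and help planners persuade the health ministry to plan preventive services nationally. A prevalence labelled with the wrong population would carry into that use.

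A second, smaller issue sits inside the eligible population. Districts are drawn with equal probability and the same number of schools is taken from each, so pupils in districts with few eligible schools have a higher chance of selection. If prevalence also differs with the number of schools in a district, a plain percentage drifts away from the provincial value for eligible pupils.

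**Working it through.** **Step 1. Target against reach.** The plan gives no figure for this point, so the texts are set side by side.

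| Dimension | Claimed | Can be sampled |
|---|---|---|
| Age | 10-19 (definition of key terms) | 10-14 (4.3, 4.5) |
| Schooling | Not restricted (Objective 1) | Grade 8 only (4.5, 4.8.2) |
| School type | Not restricted | Mixed day schools, no special-need schools, none in another oral health programme (4.8.1) |
| Oral status and needs | Not restricted | Four listed conditions excluded (4.8.2) |
| Area | Copperbelt (Objective 1), Zambia (4.2) | Copperbelt only, three of ten districts (4.5) |

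Two kinds of gap must be kept apart. Adolescents aged 15-19, those out of school, other grades, excluded school types and other provinces have selection probability zero, and no weighting or modelling within the sample recovers them. The seven districts not drawn are different: they had a chance of selection, so inference to eligible pupils in the whole province is legitimate but imprecise.

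**Step 2. The Protocol's own evidence.** Section 4.2 asserts that the province is typical and offers no comparison with national figures. Sections 1.1 and 3.0 report that caries, plaque and gingivitis vary with residence and socioeconomic status. That makes typicality something to be shown.

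**Step 3. Selection probability.** Let M be the number of eligible schools in a district and k the number taken. All eligible pupils in a chosen school may take part, so a pupil's probability is (3/10) x (k/M), and the design weight is (10/3) x (M/k). Section 4.2 gives 102 schools in ten districts, a mean of 10.2 before exclusions. With k = 6 and every M equal to 10.2, the probability is 0.3 x 6/10.2 = 0.176, which equals 18/102. With unequal M it varies. For assumed M of 6, 8 and 25:
- k = 6: 0.30, 0.225 and 0.072, a ratio of 25/6 = 4.2.
- k = 4: 0.20, 0.15 and 0.048, the same ratio.

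The conflict between six and four schools therefore changes the weight but not the argument.

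**Step 4. What ignoring the weights could do.** School counts and prevalence by district are not in the documents. All inputs below are assumptions, with equal pupils per school. The plain figure is the simple mean of the three prevalences, and the weighted figure is the sum of M x prevalence divided by the sum of M.

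| M | Prevalence, % | Plain, % | Weighted, % | Plain minus weighted, points |
|---|---|---|---|---|
| 10, 10, 10 | 25, 30, 40 | 31.7 | 31.7 | 0 |
| 6, 6, 25 | 30, 30, 30 | 30.0 | 30.0 | 0 |
| 6, 10, 15 | 20, 20, 35 | 25.0 | 845/31 = 27.3 | -2.3 |
| 6, 8, 25 | 20, 20, 35 | 25.0 | 1155/39 = 29.6 | -4.6 |
| 6, 6, 25 | 20, 30, 50 | 33.3 | 1550/37 = 41.9 | -8.6 |
| 6, 6, 25 | 40, 30, 25 | 31.7 | 1045/37 = 28.2 | +3.4 |

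The sign depends on whether prevalence rises or falls with the number of schools. Section 3.0 does not settle this for caries: it cites African studies with more caries in urban adolescents, others with the opposite, and one with no difference.

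**Step 5. Price of weighting.** For M of 6, 8 and 25, the largest district carries 25/39 = 64% of the weight. The variance inflation from unequal weights is 3 x (36 + 64 + 625)/39² = 1.43, so the interval is about √1.43 = 1.20 times as wide. Separately, if variance is estimated between districts, three districts leave two degrees of freedom and a 95% multiplier of 4.30 where large samples use 1.96. Weighting does not cure that.

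**The case against.** The strongest reply is that the population is disclosed. Section 4.3 states age and school year plainly, and Section 4.8 lists the exclusions, so an attentive reader knows who was studied. That stands against any suggestion of concealment. It also shows that the Protocol disagrees with itself, because Objective 1 and Section 4.2 were not brought into line.

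On weighting, a reader might infer from Section 4.12 and Appendix 6 that the prevalence will be reported unweighted. The documents do not say so. A weighted prevalence can also be given as a percentage, and weights for a baseline description may be set in a statistical analysis plan that is not shown. This objection stands: the Protocol specifies no weighting, and nothing more can be claimed. An unseen plan is no answer to the coverage gap, however, because groups with zero selection probability cannot be brought back by analysis.

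It can also be said that the issue concerns a descriptive aim only. That is right: the treatment comparison and the sample size of 1760 are not touched.

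**Conclusion.** The coverage point holds on the text alone and needs no assumption. Objective 1 and the national inference both claim more than the design can deliver. The population that the design supports is grade 8 pupils aged 10 to 14 in eligible mixed day secondary schools of Copperbelt.

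The weighting point holds as a mechanism. A fixed take of schools per district, whether six or four, is not self-weighting unless eligible school counts are equal. Its effect is unknown: zero with equal counts or equal prevalence, and otherwise in either direction. The range of -8.6 to +3.4 points comes from assumed inputs and is neither an estimate nor a bound.

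Two stronger conclusions are tempting. One is that the reported prevalence will be too low, or will be biased in a direction that district size alone decides. The documents do not support it, because the direction also depends on how prevalence varies between districts, which is not given. The other is that the figure will describe no real population. That does not follow either, since with the wording corrected it can describe the eligible pupils. The point is worth correcting but does not threaten the trial's internal validity.

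**What to change.** 1. Reword Objective 1, its row in Appendix 6 and the conclusions drawn from it to grade 8 pupils aged 10 to 14 in mixed day secondary schools of Copperbelt Province that meet the Section 4.8 criteria. Delete the sentence in Section 4.2 that extends the results to the country.
2. Reconcile the number of schools per district in Sections 4.5 and 4.7.
3. For baseline prevalence, report beside the plain percentage an estimate weighted by (10/3) x (eligible schools in the district / schools actually taken), with an interval that reflects clustering and the three districts.
4. Leave the randomised comparison unweighted.

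The cost is a few sentences and one variable computed from the list of eligible schools that is needed to draw the sample; no new data are collected. The downsides are a narrower claim and a wider interval for the weighted figure. Provincial precision stays limited by having three districts.
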